**Methods/design:**

This study is a stepped wedge cluster-randomized controlled trial. Eligible participants will be any office-worker aged 18–65 years from two Swiss organisations in the Cantons of Zurich and Aargau, working more than 25 h a week in predominantly sedentary office work and without serious health conditions of the neck. One hundred twenty voluntary participants will be assigned to 15 clusters which, at randomly selected time steps, switch from the control to the intervention group. The intervention will last 12 weeks and comprises workstation ergonomics, health promotion information group workshops, neck exercises and an adherence app. The primary outcome will be health-related productivity losses (presenteeism, absenteeism) using the Work Productivity and Activity Impairment Questionnaire. Secondary outcomes are neck disability and pain (measured by the Neck Disability Index, and muscle strength and endurance measures), headache (measured by the short-form headache impact test), psychosocial outcomes (e.g. job-stress index, Fear-Avoidance Beliefs Questionnaire), workplace outcomes (e.g. workstation ergonomics), adherence to intervention, and additional measures (e.g. care-seeking). Measurements will take place at baseline, 4 months, 8 months, and 12 months after commencement. Data will be analysed on an intention to treat basis and per protocol. Primary and secondary outcomes will be examined using linear mixed-effects models.

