Three studies showed a positive effect of an ergonomic intervention on economic burden (productivity), but no effect on the individual burden of pain or disability [10–12]. A systematic review and meta-analysis by Chen et al. [13] questioned the value of stand-alone workstation ergonomic interventions in the office for people with NP which, is supported by strong evidence of no effect. One study was in favour of a multi-component ergonomic intervention, and another in favour of low monitor angles [14, 15]. Despite this contradictory and underwhelming evidence supporting workstation ergonomics, it is generally considered best practice for the work environment and most companies now provide workstations that can be adjusted to suit each employee [16]. However, a worker’s use or non-use of these often expensive items has not been sufficiently explored.

Health promotion is a broad field inclusive of interventions targeting the physical and psychosocial aspects of the individual and the workplace. Two systematic reviews showed a positive effect of health promotion intervention on work productivity [17, 18].

Exercise is a common treatment for office-workers suffering from musculoskeletal disorders [19, 20]. Likewise, in office-workers exercises may alleviate headache [21]. A systematic review and meta-analysis showed that strengthening exercises should be favoured to endurance and stretching exercise for the treatment of NP in office-workers [22]. An Australian study examined the impact of neck exercises on workplace productivity in monetary terms specific to office-workers within participating companies [23]. This study found evidence that neck strengthening exercises and best-practice ergonomics positively influence productivity and pain [23]. Other recent studies show improved productivity with exercise-based interventions [24–28].

Independent of the mode of the intervention (neck exercise, workstation ergonomics, health promotion), adherence to an intervention still remains a huge problem. Different studies observed greater effect with higher participation, which points to a need for an intervention that additionally encourages adherence [23, 29, 30]. A way to enhance exercise adherence is the use of an exercise app [31]. Main benefits of an app are the constant availability of the exercise program and an interactive technology with feedback and reminder.

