### Intervention

The multi-component intervention will last for 12 weeks and will combine four existing evidence-based interventions. Each participant will receive all four interventions.
*Workstation ergonomics:* Participants’ workstation ergonomics will be assessed using an observation-based ergonomics assessment checklist for office-workers adapted to Swiss guidelines [36]. Based on the initial assessment, best practice ergonomics will be applied individually using existing infrastructure [23]. Topics will include for example the adjustment of the chair, desk, and monitor.*Health promotion:* Participants will attend health promotion information group workshops for approximately 1 h per week for 12 weeks. Content will include: attitudes to health and elements of success (including sleep); basic anatomical knowledge; behaviour change towards success; common workplace mental health issues; conflict management and resilience in the workplace; job stress and how to deal with it; keeping active (sit less, move more); keeping up the momentum and motivation; practical healthy eating; role of digital media; self-esteem; stress and relaxation workshop; and text-neck and how to avoid it [23, 37]. ‘Text-neck’ describes mechanical exposures on the neck, including static loading, non-neutral postures, and repetitive motions, associates with viewing portable devices over prolonged periods of time. The topics were selected in consultation with the organisations and on the basis of previous studies [23].*Neck exercise:* Participants will receive an individual progressive exercise programme aimed at conditioning the muscles of the neck and shoulder girdle. The exercises will be performed in groups (maximum of 12 per group) at the workplace in a dedicated room, for approximately 1 h (3 × 20 minutes) per week; once per week supervised by a physiotherapist, a human movement scientist, or a health scientist, and twice per week self-administrated. A standard sequence of exercises will be prescribed to all participants, but their implementation and progression will be within the specific capabilities of the individual considering potential age- and gender-specific requirements. Participants will perform shoulder girdle exercises (bilateral shoulder shrugs; bilateral scapular raise; bilateral incline shoulder external rotation in squat position; bilateral shoulder extension; shoulder row; bench dips; incline push-ups), progressing from un-resisted to resisted utilising variable resistance bands, and neck exercises (using the hand to apply resistance during neck flexion, extension and rotation) [38, 39]. Training load for each individual will be based on their one-repetition maximum (1-RM) that will be assessed during physical examination of the neck and regularly re-evaluated [40, 41]. Training sessions will start with ten repetitions at 50% of 1-RM warm-ups, followed by two to three sets of 10–15 repetitions of exercise at 60–80% of 1-RM corresponding to 10-RM. Adequate breaks will be taken between sets to avoid overexertion. Warm-up exercises (bilateral shoulder circling; upper body rotation) once each for 20 s, and cool-down exercises (lateral neck stretch; neck extensor stretch; seated side stretch; self-massage of shoulder and neck with spiky ball) for three times 20 s will complete the program [20, 42].*Adherence to intervention:* Workshop session attendance will be recorded as an indication of adherence to health promotion. Adherence to neck exercises will be recorded with the Physitrack® app (London, United Kingdom). Participants will maintain a record of exercise frequency, intensity, time, and type (F.I.T.T principles) [43]. A detailed instruction of each exercise technique (video), load intensity, and details regarding the number of sets and repetitions are recorded for each participant on the app enabled on their smartphone, tablet, or desk-top computer. Training reminder and feedback will be provided by the app.

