#### Secondary outcomes

Several secondary outcomes will be measured, which can be divided into the following subsections:
*Physical and health outcomes* including self-assessment of NP and headache (extent / pain drawings, occurrence, frequency, intensity, duration, Neck Disability Index, short-form headache impact test), physical examination of the neck (muscle strength, muscle endurance, mobility, local pain pressure threshold), physical activity level (International Physical Activity Questionnaire) and health related quality of life (EuroQoL Five Dimension) [49–71].*Psychosocial outcomes* as the job-stress index, job satisfaction, and health beliefs (Fear-Avoidance Beliefs Questionnaire) [47, 72–74].*Workplace outcomes* as workstation ergonomics (observation-based ergonomics assessment checklist for office-workers adapted to Swiss guidelines), workplace implementation, psychosocial workplace factors (Copenhagen Psychosocial Questionnaire), work breaks, and daily use of personal smartphone [36, 75].*Adherence to intervention*

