#### Data analysis

The effect of the intervention in reducing the productivity loss over the study period will be examined using linear mixed-effects models, similar to the one used in the simulation-based power calculation. Moreover, the broader category of generalized linear mixed-effects models will be used for the analyses of secondary outcomes. We will also investigate the distribution of gender and symptom characteristics (like persistence) across different groups at baseline. In case of uneven distributions, these factors will be included in the model to adjust for their potential confounding effects. If required, we will also adjust for other potential confounding effects in the analyses, such as age, occupation, adherence, psychosocial factors, health beliefs, job satisfaction, and physical activity at baseline.

All statistical analyses will be performed using Stata® (Texas, USA) or R® (Boston, USA) statistical software. Significance level was set at alpha = 0.05. Missing data will be examined to determine its randomness and addressed with multiple imputations, if required. The results of the mixed-effects modelling will be presented in outcome specific effect sizes and their 95% confidence intervals. The data will be analysed on an intention to treat and per protocol basis. Drop-outs before study commencement will be replaced by recruitment of new subjects.

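### Adherence is named as a possible confounder in the effect models, but it exists only after the switch to intervention and should not be adjusted for in an intention-to-treat analysis

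*Protocol article*

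**What the plan says.** The Data analysis section of the protocol article sets out the primary analysis: "The effect of the intervention in reducing the productivity loss over the study period will be examined using linear mixed-effects models". The model is to resemble the one behind the sample size. The section then adds "If required, we will also adjust for other potential confounding effects in the analyses", and the examples that follow are "such as age, occupation, adherence, psychosocial factors, health beliefs, job satisfaction, and physical activity at baseline". The analyses are to be run both by intention to treat and per protocol, and the sentence on adjustment does not separate the two.

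Three other sections bear on what adherence is:

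- **Intervention.** "Workshop session attendance will be recorded as an indication of adherence to health promotion", and "Adherence to neck exercises will be recorded with the Physitrack® app".
- **Secondary outcomes.** The list ends with "Adherence to intervention". The abstract also places it among the secondary outcomes.
- **Background.** The case for the app rests on earlier findings: "Different studies observed greater effect with higher participation".

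**The concern.** A confounder of a randomised comparison must precede allocation or be unaffected by it. Adherence as measured here is neither. It counts attendance at the intervention's own workshops and performance of the intervention's own exercises, so a cluster still under control has nothing to adhere to. The authors also expect it to carry part of the effect, which makes it a likely mediator.

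Conditioning on such a variable in the model for the treatment effect changes what the treatment coefficient means. If the recorded value is zero in control periods and positive afterwards, the coefficient is the effect of switching for someone who does not adhere. It is no longer the average effect of being switched, which is what an intention-to-treat analysis should estimate. A useful intervention could then look weak or ineffective, or a real effect could be missed through lost precision.

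**Working it through.** **The plan's own figure.** The Sample size calculation section states 72 participants, 12 clusters and three steps for 80% power to detect 5 points. Power for the closed-cohort model is Φ(5/SE − 1.96), taking alpha 0.05 as two-sided. No outcome SD is given, so the figure can be neither confirmed nor refuted. Over the stated intraclass correlations (0.1 or 0.2 for cluster, 0.2 or 0.3 for subject) and two readings of the subject correlation, 80% power needs a total SD of about 9.3 to 11.5 points. The point below does not depend on this, but it shows that the SDs of 10 and 12 assumed here are of a plausible order. The model behind the figure has no adherence term.

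**Inputs from the article.** 15 clusters, 120 participants (15 × 8), four measurements, baseline productivity 90%, effect 5 points, correlations 0.1 and 0.2.

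**Inputs assumed.** Outcome SD, the distribution of adherence, and the share *d* of the effect that works through recorded adherence.

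**Algebra.** Let *X* be 1 after the switch and 0 before, and let *a* be a person's adherence, with mean 0.6. Let the effect of switching be

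5 × [(1 − d) + d × a/0.6].

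Its average is 5 × [(1 − d) + d] = 5 for every *d*. If adherence is entered as recorded, *A* = *a* × *X*, the same effect is written as

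5(1 − d) × X + (5d/0.6) × A.

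The coefficient on *X* is therefore 5(1 − d): 5 when d = 0, 2.5 when d = 0.5, and 0 when d = 1.

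**Simulation A** (1,500 trials per row, SD 12, adherence Beta(3,2) with mean 0.6). Cells show mean treatment coefficient (empirical SE; share of trials significant).

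| Share through adherence | No adherence term | Adherence as recorded (0 under control) | One constant value per person |
|---|---|---|---|
| None | 5.05 (1.65; 85%) | 5.06 (2.86; 40%) | 5.05 (1.66; 85%) |
| Half | 5.06 (1.63; 87%) | 2.59 (2.88; 14%) | 5.06 (1.63; 87%) |
| All | 5.01 (1.64; 85%) | −0.01 (2.84; 4.5%) | 5.00 (1.64; 85%) |

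The simulated means match the algebra. Where there is no mediation, the loss is one of precision: 5/1.65 = 3.03 against 5/2.86 = 1.75, because *A* and *X* are strongly correlated.

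**Simulation B** (400 trials, SD 10, mean adherence 0.7, whole effect through adherence). The means are 5.07 without adherence, −0.02 with adherence as recorded and 5.07 with a constant value per person. The SEs are 1.44, 2.97 and 1.45.

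**Sensitivity.** Simulation A was repeated with people who adhere more also having higher productivity throughout (10 points per unit of adherence, an assumption). The coefficient with adherence as recorded is then 0.99, −1.38 and −3.74 for none, half and all. The other two models stay at about 5.

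**The case against.** Several counter-arguments have force.

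- **The default model leaves adherence out.** The primary model is to resemble the power model, which has only time, treatment and random effects. Adherence enters only if required, as one example among several. This stands. A reader might infer that the primary result will cease to be an intention-to-treat estimate, but the text supports only that it could.
- **The fall from 5 to 0 is an extreme.** It needs adherence entered as recorded and the whole effect acting through it. The Intervention section also includes individual workstation ergonomics, for which no adherence record is described, so part of the effect can bypass the covariate. This stands, and the range from 0 to 5 is the fair statement.
- **Coding of covariates is usually left to the analysis plan.** This also stands. The open coding is not a fault in itself. The fault is naming adherence as a confounder.
- **The words on baseline at the end of the list may govern every item.** For psychosocial factors, health beliefs, job satisfaction and physical activity this is a fair reading, and adjustment for them is then legitimate. A reader might infer that these items too are post-switch outcomes, but the text does not require that. The reading cannot rescue adherence, which has no baseline value.
- **Dropout.** A reader might infer that a constant value per person would lose control rows from people who leave before their switch. That presumes complete-case deletion. The Data analysis section provides for multiple imputation if required, and the simulations had no dropout, so no such loss is shown.

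**Conclusion.** The article names a wrong adjustment variable. By its own definitions adherence arises after the switch, is an outcome and is expected to carry part of the effect, and nothing keeps it out of the intention-to-treat model.

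The consequence is conditional. If adherence is entered as recorded, a true effect of 5 points is estimated at about 0 with full mediation and about 2.6 with half. With no mediation the estimate stays at about 5, but power falls from about 85% to 40%. If it is entered as one value per person, the estimate stays near 5. The full-mediation result was obtained at both SD 10 with mean adherence 0.7 and SD 12 with mean adherence 0.6; the half- and no-mediation results and the power figures rest on the latter setting alone. None of these SDs, adherence levels or mediation shares is given in the article.

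**What to change.** In the Data analysis section:

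1. Delete adherence from the adjustment list for the intention-to-treat models.
2. State that the baseline qualifier applies to every remaining time-varying covariate in the list: psychosocial factors, health beliefs, job satisfaction and physical activity.
3. Report adherence only descriptively, or in a per-protocol or dose-response analysis labelled as separate from the intention-to-treat result.

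Tying the covariates to baseline is enough. A stricter rule, such as measurement before allocation is known, could exclude the trial's own baseline data, because the section on allocation mentions notifying participants before collecting those data. An instrumental-variable analysis with the switch as instrument is not recommended: it would need the switch to act only through recorded adherence, which is doubtful given the ergonomics component.

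The cost is a sentence or two of text, with no change to data collection or sample size.

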#### Data deposition and curation

All anonymized study data will be archived at Zurich University of Applied Sciences (ZHAW) for a minimum of 10 years after study termination or premature termination of the clinical trial on restricted data pools and fire-proofed lockers, respectively with access only by study personnel.

### Sample size calculation

Based on the baseline results of an Australian study, we assumed a baseline productivity of 90% and an intervention attributable increase in productivity of 5% [23]. Also, in line with the Australian study, the cluster size was set to seven subjects. In order to test the sensitivity of the sample size calculations, we used varying cluster-specific and subject-specific intraclass correlations (Rho [1] = 0.1 or 0.2 and Rho [2] = 0.2 and 0.3 respectively) as well as varying number of steps (three or four steps). The underlying statistical model that was used in the simulations was a standard closed cohort mixed effects model comprising a random effect for the clusters, a random effect for the repeated measurements on the same cohort of individuals, a fixed effect to account for time trends, and a fixed effect representing the treatment effect [77, 78]. The linear mixed effect method from the R-package lme4 was used to estimate the models [79]. Furthermore, the acceptable probability for a Type I Error to occur was set to alpha = 0.05 and the acceptable probability for a Type II Error to occur was set to beta = 0.20 (Power = 0.80). From the four assessed scenarios, the solution with 72 participants, 12 clusters and three steps are optimal in the sense that three steps put much less burden on participants than four steps, i.e., there are less measurements per subject.

An Australian study reported an attrition rate of nearly 20%. In order to prevent the risk to under-power our study, we will increase the number of clusters from 12 to 15 (> 20%) and the number of subjects per cluster from 6 to 8 (> 20%) [23]. Consequently, we aim to enrol and follow 120 participants in 15 clusters over four measurements (one baseline and three steps from the control to the intervention arm of the study) which yields a total of 420 observations.

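### The one mixed model the protocol describes has no cluster-by-period effect; if correlation within work groups fades over time, its type I error exceeds 5% and its planned power is optimistic

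*Protocol article*

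**What the plan says.** Under Sample size calculation, the protocol article describes the simulation model term by term: "a random effect for the clusters, a random effect for the repeated measurements on the same cohort of individuals", then "a fixed effect to account for time trends, and a fixed effect representing the treatment effect". It mentions no cluster-by-period effect, decaying correlation or robust variance. Under Data analysis, the primary outcome is to be examined with "linear mixed-effects models, similar to the one used in the simulation-based power calculation", and "Significance level was set at alpha = 0.05".

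Other sections give the setting:
- The productivity questionnaire asks about the past 7 days (Primary outcome).
- Assessments are 16 weeks apart (Timeline).
- Cluster members share a floor, room or work group (Allocation to cluster and group).
- The final design has 15 clusters, 120 participants and four measurements; the cluster correlation is 0.1 or 0.2 and the subject correlation 0.2 or 0.3 (Sample size calculation).

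**The concern.** A cluster intercept and a participant intercept make the correlation between two colleagues the same whether they are measured in the same week or eight months apart. Each measurement here is a one-week snapshot. Anything that moves a whole work group in that week, and not at the next occasion, is extra variance at the level of cluster by period.

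Treatment in a stepped wedge also varies only at that level. A model without the term reads the shared movement as independent individual noise and divides it by the cluster size. The standard error of the treatment effect is then too small, the 95% interval too narrow, and the false positive rate on the primary outcome above the stated 0.05. A power simulation run on the same model is optimistic for the same reason.

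**Working it through.** **The plan's own figure.** The plan gives 72 participants in 12 clusters for 80% power to detect a 5-point gain. This cannot be reproduced, because no standard deviation is given. It holds if the total SD is about 9.3 to 11.6 points, depending on the correlations and how they are read. The SD matters for power only; the type I error below does not depend on it.

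**Inputs from the protocol.** I = 15 clusters, m = 8, T = 4 periods, three sequences, Rho1 = 0.1 or 0.2, Rho2 = 0.2 or 0.3.

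**Assumptions.** Five clusters per sequence, no attrition, normal outcome, two-sided test at 1.96, total variance 1. Cluster autocorrelation c is 1.0, 0.9, 0.8 or 0.5. Rho2 is read both as additional to Rho1 and as including it.

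**Variance components (additive reading).** Cluster Rho1·c; cluster-by-period Rho1·(1 − c); participant Rho2; residual 1 − Rho1 − Rho2.

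**Variance of the treatment effect.** Let τ² be cluster variance plus participant variance/m, and σ² be residual variance/m plus any cluster-by-period variance. Then

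Var = I·σ²(σ² + Tτ²) / [(IU − W)σ² + (U² + ITU − TW − IV)τ²].

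- U = 5(3 + 2 + 1) = 30; W = 5² + 10² + 15² = 350; V = 5(9 + 4 + 1) = 70.
- IU − W = 450 − 350 = 100; U² + ITU − TW − IV = 900 + 1800 − 1400 − 1050 = 250.
- So Var = 15σ²(σ² + 4τ²)/(100σ² + 250τ²).

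**Worked case: Rhos 0.1/0.2, c = 0.8.**
1. True components: cluster 0.08, cluster-by-period 0.02, participant 0.20, residual 0.70.
2. The two-intercept model settles at residual 0.70 + 0.02 = 0.72, participant 0.20 − 0.02/4 = 0.195 and cluster 0.08 + 0.02/4 = 0.085.
3. Variance it reports: σ² = 0.72/8 = 0.09, τ² = 0.085 + 0.195/8 = 0.1094, so Var = 0.01959.
4. Best attainable true variance: σ² = 0.70/8 + 0.02 = 0.1075, τ² = 0.08 + 0.20/8 = 0.105, so Var = 0.02299. The two-intercept estimator itself has true (sandwich) variance 0.02305.
5. Ratio 0.02305/0.01959 = 1.18. Type I error = 2Φ(−1.96/√1.18) = 7.1%.

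**All cases.**

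| Autocorrelation | Rhos 0.1/0.2: ratio, error | Rhos 0.2/0.3: ratio, error | Range over all four Rho pairs, both readings |
|---|---|---|---|
| 1.0 | 1.00, 5.0% | 1.00, 5.0% | 5.0% |
| 0.9 | 1.09, 6.0% | 1.26, 8.1% | 5.9%-8.1% |
| 0.8 | 1.18, 7.1% | 1.50, 10.9% | 6.8%-10.9% |
| 0.5 | 1.41, 9.9% | 2.10, 17.6% | 9.2%-17.6% |

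**Simulation check.** REML fits of the two-intercept model, 1,500 runs per setting, gave:
- c = 1.0: 4.1%-5.7%
- c = 0.9: 6.1%-8.5%
- c = 0.8: 7.1%-7.9% (Rho1 0.1) and 9.4%-11.5% (Rho1 0.2)
- c = 0.5: 9.9%-12.3% (Rho1 0.1) and 14.9%-17.4% (Rho1 0.2)

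**With the cluster-by-period term fitted (c = 0.8 and 0.5).** Simulated error was 4.8%-5.9% with a z test, 4.3%-5.8% with t on about 41 df (60 − 15 − 3 − 1), and 3.3%-3.7% with t on 13 df.

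**Power.** Take the SD that gives 80% at 12 clusters of 6 (10.04 to 11.55, additive reading). With the true variance, 15 clusters of 8 have about 95% power at c = 1.0, 82%-91% at 0.8 and 65%-85% at 0.5. With 6 remaining per cluster, the figures are 88%, 74%-84% and 60%-78%.

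**The case against.** The strongest reply is that the analysis model is not fixed. The full description belongs to the simulation, and "similar to the one used in the simulation-based power calculation" is not the same as identical to it. An analysis plan that is not shown may add the term. That stands as a limit: a reader might infer that the final analysis will certainly have only two intercepts, and the documents do not say so. It does not remove the point, because no other primary model is named and the power simulation was run on this one.

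Second, a reader might infer that the false positive rate will be 8% to 18%. The documents do not support that. They give neither an autocorrelation nor a cluster-by-period variance. The error is nominal at 1.0, and the top of the range needs autocorrelation 0.5 together with the higher correlations.

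Third, it is tempting to blame the small number of clusters. The same 15 clusters give about 5% when cluster-by-period variance is absent.

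Fourth, the mechanism is plausible but not documented. The outcome counts only neck-pain-related loss, and vacation hours are recorded in an item that does not enter the score, so general workplace events would have to act through neck pain. Group delivery is weak support: "The exercises will be performed in groups (maximum of 12 per group) at the workplace in a dedicated room" applies only during the intervention, and groups of up to 12 are larger than a cluster, so exercise groups need not be the clusters.

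Finally, power at autocorrelation 0.8 stays above 80% with all 120 participants. That is correct before attrition; with 6 per cluster it no longer holds for every pair of correlations.

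**Conclusion.** The point holds conditionally. The only model the protocol describes assumes a within-cluster correlation that does not change over time, and the primary analysis is tied to it by similarity. How far the error exceeds 5% depends wholly on the autocorrelation, which is an assumption here. The figures also rest on equal sequences, complete data, a normal outcome and clusters of 8; the protocol elsewhere defines clusters of seven, which would lower the inflation somewhat. This is an inexpensive improvement to a stated method, not proof that the planned test is invalid.

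**What to change.** - Pre-specify the primary model with random intercepts for cluster, cluster-by-period and participant, period as a factor, and the treatment effect.
- Test the treatment effect with Kenward-Roger or Satterthwaite degrees of freedom. The contrast between t on 41 and t on 13 df shows that the choice matters and should be named in advance.
- Report the two-intercept model as a sensitivity analysis.
- Rerun the power simulation over autocorrelations of, for example, 0.5 to 1.0, state the SD used, and restate power.
- Organisation and organisation-by-period fixed effects are optional. They were not in the model behind the error rates above, and their cost is unknown because the split of clusters between the two organisations is not given.

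The cost is a change of analysis wording and one simulation rerun. In simulation at SD 10, the mean standard error rose from 1.38 to 1.43 (about 4%) when no cluster-by-period variation existed. At autocorrelation 0.8 it rose from 1.38 to 1.50 (9%, Rhos 0.1/0.2) and from 1.24 to 1.51 (22%, Rhos 0.2/0.3), so intervals will be wider where the variation is real.

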#### Allocation to cluster and group

The project coordinator will allocate eligible participants to a cluster (de-identified) until the required number is reached for each intake. A senior statistician blinded to the identity of individuals will randomise clusters to a sequence within the period of data collection when clusters change from the control to the intervention condition (group 1 to 3). A cluster is defined as a group of seven office-workers located on the same floor, room or work group. Fifteen clusters will be required to achieve a sample size of 120. The study coordinator will notify individuals of their allocation, collect baseline data, and communicate between participants and the intervention health professional to organize assessments.

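### The planned size contradicts itself: 15 clusters of seven give 105 participants, not 120; 120 participants measured four times give 480 observations, not 420; and the simulated cluster size is given as both seven and six.

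*Protocol article*

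**What the plan says.** The figures come from three places in the protocol article.

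- **Abstract, Methods/design:** 120 participants in 15 clusters, measured at baseline and at 4, 8 and 12 months.
- **Allocation to cluster and group:** "A cluster is defined as a group of seven office-workers located on the same floor, room or work group". The next sentence reads "Fifteen clusters will be required to achieve a sample size of 120".
- **Sample size calculation, first paragraph:** "in line with the Australian study, the cluster size was set to seven subjects". After the simulations it reports that "the solution with 72 participants, 12 clusters and three steps are optimal".
- **Sample size calculation, second paragraph:** citing attrition of nearly 20% in an earlier Australian study, it raises the clusters from 12 to 15 and "the number of subjects per cluster from 6 to 8 (> 20"%). It then plans to enrol and follow 120 participants in 15 clusters at four measurements (baseline plus three steps), "which yields a total of 420 observations".

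**The concern.** Participants, clusters, cluster size, measurements and observations are tied together by multiplication, and the stated values do not multiply out. Two adjacent sentences in the allocation section disagree on the total. One sentence in the sample size section disagrees with itself on the number of observations. The input and the output of the simulation disagree on cluster size.

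Two things are at stake. First, the coordinator allocates participants until a required number is reached, and that number differs by 15 depending on whether the cluster definition or the total is followed. Second, cluster size affects precision in a stepped wedge design. A reader who cannot tell whether six or seven per cluster was simulated cannot identify or repeat the calculation that met the 80% power criterion.

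**Working it through.** **Inputs, all from the protocol article**

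- Cluster size by definition: 7 (Allocation to cluster and group).
- Cluster size set for the calculation: 7 (Sample size calculation).
- Chosen solution: 72 participants, 12 clusters (Sample size calculation).
- Planned change: clusters 12 to 15, size 6 to 8 (Sample size calculation).
- Enrolment: 120 participants, 15 clusters (Abstract and both sections).
- Measurements per participant: 4 (Abstract and Sample size calculation).
- Stated observations: 420 (Sample size calculation).
- Attrition: taken as 20%; the text says nearly 20%.

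**Formulas:** participants = clusters x cluster size; observations = participants x measurements.

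**1. Reproducing the plan's figures with 15 clusters and 4 measurements**

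| Cluster size | Participants | Observations | Matches 120? | Matches 420? |
|---|---|---|---|---|
| 6 | 15 x 6 = 90 | 90 x 4 = 360 | no | no |
| 7 | 15 x 7 = 105 | 105 x 4 = 420 | no | yes |
| 8 | 15 x 8 = 120 | 120 x 4 = 480 | yes | no |

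No cluster size gives both. For both to be true, each participant would need 420 / 120 = 3.5 measurements.

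**2. Could 420 be a count net of attrition?**

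- 20% missing throughout: 480 x 0.8 = 384.
- Full baseline, then 20% missing at all three follow-ups: 120 + 3 x 96 = 408.
- Linear loss reaching 20% at the last visit: 120 + 112 + 104 + 96 = 432.
- Three measurements instead of four: 120 x 3 = 360.

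None gives 420.

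**3. The simulated design**

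- Chosen solution: 72 / 12 = 6 per cluster. The starting value in the planned increase is also 6.
- At the stated size of seven, 12 clusters would be 12 x 7 = 84.

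The stated input is therefore 7, and the reported solution is 6.

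**4. Size of the gap**

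- Participants: 120 - 105 = 15; 15 / 120 = 12.5%.
- Observations: 480 - 420 = 60; 60 / 480 = 12.5%.

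**5. Does the gap threaten the head count after attrition?**

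- If 72 is the required number: 72 / 0.8 = 90. Both 105 and 120 exceed it, and 20% loss leaves 105 x 0.8 = 84 or 120 x 0.8 = 96.
- If seven per cluster was simulated, so that 84 is required: 84 / 0.8 = 105. A target of 105 just meets it, and 120 exceeds it.

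**6. The two remarks that the increases exceed 20%**

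- Clusters: 15 / 12 = 1.25, an increase of 25%.
- Cluster size: 8 / 6 = 1.33, an increase of 33%.

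Both remarks are true as printed.

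**The case against.** The strongest reply is that the intended design is clear enough. The total of 120 in 15 clusters appears in the abstract and in both sections, and the sample size section raises the cluster size to eight. On that reading, the seven in the cluster definition and the 420 are leftovers, and staff would still work to the stated target of 120. Much of this stands. The text does lean towards 15 x 8, and it would be too strong to say that recruitment will stop at 105. But seven is given as a definition, and 420 as the product of enrolling and following 120 people. Neither is marked as an average or as net of loss. This reply also leaves open whether six or seven was simulated.

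A reader might go further and infer three things that the document does not support.

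- **That the attrition step is wrong because 72 / 0.8 = 90, not 120.** The article never claims to inflate to exactly 90. It says each increase exceeds 20%, which is true, and enrolling above the minimum is a cautious choice.
- **That the 80% power is misstated for the enrolled design.** The criterion belongs to the simulated design before the allowance for attrition. An enlarged design with more than 80% power at full retention is what such an allowance normally produces.
- **That the trial is under-powered.** The head counts above show no shortfall. The article gives no standard deviation, so power can only be examined by assumption. Suppose the standard deviation is whatever gives 12 x 6 exactly 80% power for 5 points: about 10.0 to 11.5 if the two intraclass correlations are additive variance shares, or about 9.5 to 9.9 if the second includes the first. Power with complete data is then about 92% at 15 x 7 and 95% at 15 x 8. After 20% loss it is about 86% and 90%. All are above 80%.

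**Conclusion.** The point holds as an internal contradiction in the planned size. With 15 clusters and four measurements, 120 participants and 420 observations cannot both be right, and a cluster of seven cannot give 120. The simulated cluster size is stated as seven and implied as six, so the design that met the 80% power criterion is unclear. The discrepancy is 15 participants and 60 observations, 12.5% of each planned total. These conclusions use only printed figures and multiplication.

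The consequence is limited. The contradiction makes the enrolment target and the power calculation ambiguous, but it does not show that the trial is too small or that the allowance for attrition is inadequate. That reassurance assumes loss of about 20% of participants, as the article does.

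**What to change.** Carry one design through the article.

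- **If 120 in 15 clusters is intended**, which the repeated statements favour: define a cluster as eight in Allocation to cluster and group, and replace 420 by 480 in Sample size calculation. The two remarks that the increases exceed 20% can stay.
- **If seven per cluster is intended:** restate the target as 105 wherever 120 appears, keep 420, and correct the planned increase from six to eight. From six to seven is only 7 / 6 - 1 = 16.7%, so the remark attached to that increase would have to change with it.
- **In either case:** state in Sample size calculation the cluster size that was simulated, either six with 72 participants or seven with 84.

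The cost is a text correction. A rerun of the existing simulation is needed only if the records do not show which cluster size was used. Keeping the target of 120 adds no participants.
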